##### Blood samples

Blood samples will be collected on the same way as blood samples in the clinical routine in our hospital. The samples will be analyzed in the hospital’s central laboratory. Since only parameters will be assessed that are available in clinical routine, no study-specific procedures need to be put in place. Table 3 lists the parameters that will be assessed.

**Table 3 Tab3:** Laboratory parameters assessed at different time points during the study

	0 h	72 h	7 days*
Leukocytes [thous./μl]	x	x	x
Thrombocytes [thous./μl]	x	x	x
Red cell distribution with [%]	x	x	x
Hemoglobin [g/dl]	x	x	x
Hematocrit [%]	x	x	x
Lymphocytes [thous./μl]	x	x	x
Neutrophils [thous./μl]	x	x	x
Monocytes [thous./μl]	x	x	x
INR	x	x	x
PTT [sec.]	x	x	x
D-dimers [mg/l]	x	x	x
Fibrinogen [mg/dl]	x	x	x
Ferritin [ng/ml]	x	x	x
Urea [mg/dl]	x	x	x
Creatinine [mg/dl]	x	x	x
Uric acid [mg/dl]	x	x	x
LDH [U/l]	x	x	x
CK [U/l]	x	x	x
CK-MB [U/l]	x	x	x
Myoglobin [U/l]	x	x	x
Troponin T [ng/ml]	x	x	x
ProBNP [pg/ml]	x	x	x
AST [U/l]	x	x	x
ALT [U/l]	x	x	x
AP [U/l]	x	x	x
g-GT [U/l]	x	x	x
Bilirubin [mg/dl]	x	x	x
Bilirubin direct [mg/dl]	x	x	x
Bile acids [μmol/L]	x	x	x
CRP [mg/l]	x	x	x
PCT [ng/ml]	x	x	x
Protein [g/dl]	x	x	x
Albumin [g/dl]	x	x	x
IL-6 [pg/ml]	x	x	x
TNF-α	x	x	x
Triglycerides [mg/dl]	x	x	x
Cholesterine [mg/dl]	x	x	x
LDL-cholesterine [mg/dl]	x	x	x
HDL-cholesterine [mg/dl]	x	x	x
IgG [mg/dl]	x	x	x

*Parameters after 7 days will only be collected, if they are available within clinical routine. No additional blood samples will be taken

In all patients with CRRT, point-of-care blood gas analysis testing will be performed at least every 4–6 h as part of clinical routine assessments (available parameters: pH, pCO2 [mmHg], pO2 [mmHg], sO2 [%], SBC [mmol/l], Hb [g/dl], Na [mmol/l], K [mmol/l], Ca [mmol/l], Cl [mmol/l], lactate [mmol/l], glucose [mmol/l], bilirubin [mmol/l]). The results from these analyses, including serum bilirubin concentrations, will be available from the patient files and retrieved from the patient records for assessment in this trial. In the no CRRT group, these parameters will most likely not be available for all patients, since not all will require an arterial vascular access and repeated point-of-care blood gas analysis testing.

In addition to routine parameters and peripheral blood mononuclear cells (PBMC), small amounts of patient serum will be collected, frozen at – 80 °C and stored in a specifically designated refrigerator. After enrollment of all patients, all samples will then be sent to an external laboratory (Olink Proteomics, [name], Sweden). If sample residues remain after analysis, they will be discarded and disposed of properly. The samples are anonymized for dispatch, so that no conclusions can be drawn about individual patients in the external laboratory.

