Study type	Interventional Allocation: randomized; Intervention model: parallel assignment; Masking: open-label Primary purpose: treatment of severe acute-on-chronic liver failure Post-approval/pivotal study
Date of first enrollment	December 12, 2021
Target sample size	51
Recruitment status	Recruitment phase
Primary outcome(s)	Serum bilirubin reduction after 72 h
Key secondary outcomes	• Survival time (days) from baseline • Interleukin-6 after 72 h • Liver function parameters (72 h): Quick/INR, AST, ALT, AP, g-GT • Blood lactate (72 h) • Clinical scores: CLIF-SOFA-score, MELD score, SOFA score, SAPS II and FIPS score (72 h) • Ventilator free days (VeFD) in the first 30 days after randomization, where each day on invasive mechanical ventilation (IMV), non-invasive ventilation (NIV), or ECMO is defined as ventilator day. VeFD=0, if the patient dies in the first 30 days after randomization • Vasopressor free days (VaFD) in the first 30 days after randomization, where each day with any dose of epinephrine, norepinephrine, dobutamine, argipressin or terlipressin is defined as vasopressor day. VaFD=0, if the patient dies in the first 30 days after randomization • Dialysis free days (DFD) in the first 30 days after randomization, where each day on renal replacement therapy (RRT) is defined as dialysis day. DFD=0 if the patient dies in the first 30 days after randomization • A biomarker panel of pro- and anti-inflammatory cytokines (blood samples will be frozen and stored for later analyses, panel will be determined at the time of analysis)
1.3. **Protocol version**	
Version 1.3, 27.01.2022 Revision chronology:	
	• Version 1.0; submitted to IRB for approval (02.07.2021); revision requested by IRB (05.08.2021) • Version 1.1; revised version, considering previous request by IRB (09.08.2021); IRB approval (17.08.2021) • Version 1.2.; amendment submitted to IRB (04.10.2021); addition of trial registration information, specification of randomization tool; IRB approval (19.10.2021)

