##### Secondary endpoints

Survival time (days) from baselineInterleukin-6 after 72 hLiver function parameters (72 h): Quick/INR, AST, ALT, AP, g-GTBlood lactate (72 h)Clinical scores: CLIF-SOFA-score [38], MELD score [39], SOFA score [40], SAPS II [41], and FIPS score [42] (72 h)Ventilator-free days (VeFD) in the first 30 days after randomization, where each day on invasive mechanical ventilation (IMV), non-invasive ventilation (NIV), or ECMO is defined as ventilator day. VeFD=0 if the patient dies in the first 30 days after randomizationVasopressor free days (VaFD) in the first 30 days after randomization, where each day with any dose of epinephrine, norepinephrine, dobutamine, argipressin or terlipressin is defined as vasopressor day. VaFD=0 if the patient dies in the first 30 days after randomizationDialysis-free days (DFD) in the first 30 days after randomization, where each day on renal replacement therapy (RRT) is defined as dialysis day. DFD=0 if the patient dies in the first 30 days after randomizationA biomarker panel of pro- and anti-inflammatory cytokines (blood samples will be frozen and stored for later analyses, the panel will be determined at the time of analysis)

Mean serum bilirubin levels and clinical scores at 72 h will be compared between treatment groups. Medians will be compared for other laboratory outcomes at 72 h. Survival times will be compared based on estimated hazard ratios and inspection of Kaplan-Meier curves. VeFD, VaFD, and DFD will be summarized by medians and compared between treatment arms based on the estimated probability of a better outcome (C-Index).

The primary endpoint and the secondary endpoints were selected for their relevance in the context of ACLF. Bilirubin is a core parameter describing disease severity and progression in ACLF. Bilirubin measurements are widely available. Previous retrospective analyses of patients with ACLF treated with CytoSorb described the course of bilirubin and these findings could therefore be used for the sample size estimation for this trial.

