#### Sample size

In this study, the randomization to the treatment arms CRRT with CytoSorb, CRRT without CytoSorb, and no CRRT will be done with a 1:1:1 ratio. The group with no CRRT is included merely for exploratory analysis of safety aspects and does not affect the power analysis. The sample size calculation is motivated by data from case reports and retrospective case series, according to which serum bilirubin levels in patients with liver failure could be reduced by 50% by adsorption in the CytoSorb adsorber for 72 h [17–20]. We expect a mean of 10 mg/dl serum bilirubin at baseline, no change in control patients, and a reduction to a mean of 5 mg/dl after 72 h in the cytokine adsorption group. The typical range, 1 to 20 mg/dl, implies an expected standard deviation of about 5 mg/dl. This is a conservative estimate, as the inclusion criterion, bilirubin >5mg/dl, was not considered for the calculation. On the basis of a two-group *t*-test with a two-sided significance level of 5%, a sample size of 17 patients in each group yields a power of 80% to detect a difference if it is assumed that the mean serum bilirubin levels after 72 h differ by 5 mg/dl, given a standard deviation of 5 mg/dl in both groups. This is conservative in that we anticipate a lower standard deviation after 72 h in the intervention group. No missing values up to 72 h are expected. Hence, the numbers of patients to be randomized to the three treatment arms are *n*=17:17:17.

In the unexpected event that patients die within the study before reaching the 72-h end point, we will describe an appropriate expansion of enrolment in an amendment to this study protocol.

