##### List of clinical data and blood samples to be collected

List of clinical data and blood samples to be collected is shown in Tables 2 and 3.

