Optimal timing of initiation of CRRT in AKI is a matter of ongoing debate. In the CRRT groups of this trial, CRRT will be initiated when patients reach AKI KDIGO grade 3. However, in our hospital, CRRT in AKI in general is initiated later, i.e., not before patients develop life-threatening complications, such as severe hyperkalemia or severe respiratory failure due to volume overload. In patients with ACLF, specifically, there is no clear evidence supporting an early or a late initiation strategy for CRRT. For safety reasons, we will include a third study group without CRRT as a safety control group. Patients randomized to this group will not receive early CRRT as in the other groups but the use of CRRT will be delayed until the development of one or more of the following criteria: a serum potassium level of 6.0 mmol or more per liter, a pH of 7.20 or less due to metabolic acidosis or a serum bicarbonate level of 12 mmol per liter or less, evidence of severe respiratory failure based on a ratio of the partial pressure of arterial oxygen to the fraction of inspired oxygen of 200 or less and clinical perception of volume overload. We will continuously monitor survival, complications, and safety of the treatment in all study groups to be able to detect early any potential harm related to CytoSorb treatment or early initiation of CRRT in comparison to the no CRRT group.

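### Blood lactate at 72 h is a secondary endpoint without a stated source for every no-CRRT patient, so comparisons with that arm would rest on a probably sicker subset of it

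*Protocol article*

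**What the plan says.** The synopsis table and the Secondary endpoints section both name blood lactate at 72 h. The latter also fixes the analysis: "Medians will be compared for other laboratory outcomes at 72 h".

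For laboratory data, the Blood samples section states "Table 3 lists the parameters that will be assessed", and a later section repeats: "List of clinical data and blood samples to be collected is shown in Tables 2 and 3". Table 3 has a long list of analytes at 0 h and 72 h, including LDH, bilirubin, INR and IL-6, but no lactate. Table 2 has none either. The Blood samples section adds: "Since only parameters will be assessed that are available in clinical routine, no study-specific procedures need to be put in place".

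Lactate appears as a collected value only in the paragraph below Table 3, in the list of blood gas parameters. That testing is set at a minimum of every 4–6 h for all patients with CRRT. For the third arm the same paragraph says "In the no CRRT group, these parameters will most likely not be available for all patients", because some of these patients will need neither an arterial line nor serial blood gases.

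On the role of that arm, the Sample size section says: "The group with no CRRT is included merely for exploratory analysis of safety aspects".

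**The concern.** An endpoint that is to be compared between arms needs the same source in each arm. Here two arms have a fixed blood gas schedule that covers the 72-h time point, and the third has values only where care called for them. The missing values would therefore fall mainly in one arm, for a reason linked to how ill the patient is.

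The third arm was included to pick up early signs that early CRRT or CytoSorb does harm. If its observed lactates come mainly from its sicker members, its median is too high, and the CRRT arms look better on lactate than they should. An analysis plan can describe such a gap, but it cannot recover values that were never measured.

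**Working it through.** **The plan's own figure.** The only design calculation is for 72-h bilirubin: difference 5 mg/dl, SD 5 mg/dl, two-sided 5%, 80% power, 17 per group. A two-sample t-test calculation gives n = 16.71, hence 17 per group, with power 80.7% at 17. The figure reproduces and does not depend on lactate. The protocol gives no lactate SD and no expected sampling rate.

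**Tracing the source of lactate by arm.**

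- CRRT with CytoSorb and CRRT without CytoSorb: blood gases at least every 4–6 h (Blood samples), and CRRT planned for at least 72 h (Description of study plan and interventions). The 72-h value is covered while CRRT runs.
- No CRRT, patient never starts CRRT: a value exists only if care required a blood gas.
- No CRRT, patient later starts CRRT: this happens on deterioration (Study aim and choice of comparator). The patient then comes under the CRRT blood gas schedule. This ties availability to severity more closely.
- Study draw at 0 h and 72 h, all arms: the analytes named as examples are blood count, electrolytes, kidney and liver parameters and coagulation. Lactate is not among them.

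**Illustration of size.** All inputs here are assumptions, on a scale where lactate is roughly normal. Let f be the fraction of the no-CRRT arm with a value, taken as its sickest patients, and ρ the correlation of severity with lactate. With c the standard normal quantile at 1 − f and φ the standard normal density:

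mean shift = ρ × φ(c) / f

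Example: f = 0.6 gives c = −0.253, φ(c) = 0.386, φ(c)/f = 0.644; with ρ = 0.5 the shift is 0.32 SD.

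Because the plan compares medians, the median shift was found by simulation (2,000,000 draws). The loss of precision against a full arm is the standard error ratio √(1/17 + 1/m) / √(2/17), with m = 17 × f rounded and the SD held constant.

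| f | m of 17 | Median shift, ρ = 0.3 | ρ = 0.5 | ρ = 0.7 | SE ratio |
|---|---|---|---|---|---|
| 80% | 14 | 0.10 SD | 0.17 SD | 0.22 SD | 1.05 |
| 60% | 10 | 0.19 SD | 0.32 SD | 0.43 SD | 1.16 |
| 40% | 7 | 0.29 SD | 0.48 SD | 0.66 SD | 1.31 |

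With ρ = 0 the shift is 0 at every f. The precision loss is modest by comparison and would be visible in the reported numbers. The shift would not be visible.

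**The case against.** The strongest reply is that absence from Table 3 does not prove absence from the study sample. The intervention section promises electrolytes, yet Table 3 has no sodium or potassium row, so the table is not exhaustive, and the list of analytes there is open-ended. Table 1, the schedule of assessments, is not readable here. This stands as a limit on certainty. It does not remove the point, because the Blood samples section itself says that the list containing lactate will probably be incomplete in one arm.

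It is also fair that coverage in the CRRT arms is not absolute: treatment may be stopped at any time, and deaths before 72 h can occur in any arm. The imbalance is one of schedule, not of complete against absent data.

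A reader might infer more than the documents support:

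- *That the whole safety comparison is compromised.* Lactate is not a safety endpoint. The Safety endpoints section covers adverse effects, device deficiencies and incidents, and survival to day 90 is recorded for all patients. None of these needs a blood gas.
- *That the data plan contradicts the criteria for deferred CRRT.* The section on early termination says "the use of CRRT will be delayed until the development of one or more of the following criteria", and these criteria use potassium, pH, bicarbonate and oxygenation. But the Blood samples paragraph concerns which results can be retrieved for research. Saying that not every patient needs serial blood gases is compatible with testing when a criterion is suspected.
- *That potassium comes only from blood gases.* Electrolytes are named for the study draw.
- *That the 72-h clinical scores have the same gap.* The documents do not give the score components, so this cannot be shown.

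**Conclusion.** The point holds in a limited form. Followed as written, the lactate comparison of either CRRT arm with the no-CRRT arm would use a probably sicker part of that arm. That the sampled patients are sicker is an inference, but it follows from the protocol's own reason for the missing values and from the way late CRRT is triggered.

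The size is unknown. An upward shift of about 0.1–0.7 SD in the no-CRRT median rests on assumed sampling of 40–80% and an assumed correlation of 0.3–0.7. No single value in that range can be defended from the documents, and the shift vanishes without correlation.

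The consequence is confined to one endpoint in exploratory comparisons. The Statistical methods section restricts confirmatory testing to the primary outcome, so lactate is descriptive. The primary endpoint, survival, adverse events and the comparison between the two CRRT arms are unaffected. It is worth correcting because the correction is cheap and must come before the data are collected.

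**What to change.** Add lactate to Table 3 at 0 h and 72 h for all three arms, taken from the study draw already scheduled at those times. Record for each value whether the sample was arterial or venous. Report the number of patients with a 72-h value in each arm beside the medians.

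The cost is one small tube or assay at two time points and a few eCRF fields, with no extra puncture and no extra patients. One drawback remains: the sections on blood sampling describe arterial or central venous lines in the CRRT arms, while some no-CRRT patients will have neither. Sample type will therefore differ between arms, which is why it has to be recorded.

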##### Participant retention and follow-up

As described in the “Statistical methods” section, adherence to intervention protocols and participant retention primarily depend on the treating physicians. Therefore, no specific measures need to be taken to increase patient retention. Since no specific follow-up is planned in this study, no specific measures need to be taken in this respect, either.

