**Methods:**

The CYTOHEP study is a prospective, single-center, open-label, three-arm, randomized, controlled intervention trial. Patients with ACLF and AKI stage 3 according to Kidney Disease: Improving Global Outcome (KDIGO) criteria will be randomized into three groups to be treated with (1) continuous renal replacement therapy (CRRT) and CytoSorb, (2) CRRT without CytoSorb, and (3) without both, CRRT and CytoSorb. In the hemoadsorption group, CytoSorb will be used for 72 h. The other groups receive standard of care with early or late initiation of CRRT, respectively. Primary endpoint of the study is serum bilirubin concentration after 72 h, important secondary endpoints are 30-day survival and a panel of inflammatory parameters.

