**Fig. 3 Fig3:**
[figure not shown]
Participant timeline displaying timepoints of interventions and assessments during the 30-day study period. After the end of study (day 30) survival of the study participants will be followed up until day 90. CS, CytoSorb

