### Data collection, management, and analysis

#### Data collection methods

##### Clinical data

Besides patient-specific demographic and personal data (e.g., age, height) medical pre-conditions, previous treatment in another hospital before referral to the Freiburg University Medical Center, and previous medication will be documented. Beyond this, during the study, clinical- and treatment-related data will be collected, including information on oxygen demand and ventilation parameters in patients requiring mechanical ventilation or high-flow oxygen support (see Table 2 for details) and clinical scores will be assessed at baseline and at 72 h (CLIF-SOFA-score [38], MELD score [39], SOFA score [40], SAPS II [41] and FIPS score [42]). Survival from baseline up to day 90 will be assessed for all patients. All clinical data will be retrieved from the electronic patient files (MEONA GmbH, Freiburg, Germany and COPRA System GmbH, Berlin, Germany). All clinical information collected for this study will be available from the electronic patient charts.

**Table 2 Tab2:** Clinical data collected during the study. Data will be retrieved from the hospital’s electronic patient charts

	0 h	6 h	12 h	24 h	48 h	72 h	7 days
Supply of red cell concentrates [number]	x	x	x	x	x	x	x
Supply of thrombocyte concentrates [number]	x	x	x	x	x	x	x
Supply of fresh frozen plasma [number]	x	x	x	x	x	x	x
Dosage of norepinephrine [μg/kg/min]	x	x	x	x	x	x	x
Dosage of dobutamin [μg/kg/min]	x	x	x	x	x	x	x
Dosage of epinephrine [μg/kg/min]	x	x	x	x	x	x	x
Dosage of argipressin [IE/kg/min]	x	x	x	x	x	x	x
Dosage of terlipressin [mg/h]	x	x	x	x	x	x	x
Oxygen supply (l/min)	x	x	x	x	x	x	x
In patients requiring mechanical ventilation:							
FiO_2_	x	x	x	x	x	x	x
PEEP [mbar]	x	x	x	x	x	x	x
Body temperature	x	x	x	x	x	x	x
RRsys [mmHg]	x	x	x	x	x	x	x
RRdia [mmHg]	x	x	x	x	x	x	x
Mean arterial pressure [mmHg]	x	x	x	x	x	x	x
Heart rate [1/min]	x	x	x	x	x	x	x

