The most relevant secondary endpoint is survival time from baseline since these data are planned to be used for the sample size calculation in a subsequent multi-center trial where survival time will serve as the primary endpoint. Due to the frequent application of cytokine adsorption in medical practice, a subsequent trial will be warranted even if the data of this trial will not show a benefit for cytokine adsorption. The effects of CRRT with CytoSorb versus CRRT without CytoSorb with respect to survival time will be estimated and tested by Cox regression. The regression model will include treatment and continuous baseline bilirubin level as independent variables. As an estimate of the effect size, the hazard ratio between the two treatment arms will be given with the corresponding asymptotic two-sided 95% confidence interval. Rates of patients surviving from baseline will be estimated for the three treatment arms using the Kaplan-Meier method.

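### Survival to day 90 is promised for all patients, but the protocol says no follow-up is planned and names only the hospital's own charts as data source

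*Protocol article*

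**What the plan says.** The endpoint list defines survival as "Survival time (days) from baseline", with no horizon. The abstract names a 30-day reading: "important secondary endpoints are 30-day survival and a panel of inflammatory parameters". The Fig. 3 caption separates the study period from survival follow-up: "After the end of study (day 30) survival of the study participants will be followed up until day 90". The Clinical data section makes the same commitment: "Survival from baseline up to day 90 will be assessed for all patients".

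That section then gives the source: "All clinical data will be retrieved from the electronic patient files". It adds: "All clinical information collected for this study will be available from the electronic patient charts". The section Participant retention and follow-up closes with: "Since no specific follow-up is planned in this study, no specific measures need to be taken in this respect, either".

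The statistical methods section ranks the endpoint and gives its purpose, which is planning the next, multi-center trial: "The most relevant secondary endpoint is survival time from baseline since these data are planned to be used for the sample size calculation". The analysis is Cox regression with treatment and baseline bilirubin, plus Kaplan-Meier estimates for the three arms.

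**The concern.** A promise to follow survival to day 90 in everyone cannot stand beside a statement that no follow-up is planned and no measures are needed. If the second statement governs practice, the team is left with the hospital's charts. These document care in this hospital and need not show a death at home or elsewhere.

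Patients leave hospital because they have recovered enough to do so, so discharge is related to the risk of death. Censoring them at discharge violates the non-informative censoring that Cox and Kaplan-Meier analyses require. Counting them as alive misses later deaths. Either error would carry into the planning of the follow-on trial, where survival is to be the primary endpoint.

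Ventilator-, vasopressor- and dialysis-free days are also exposed. Each is set to 0 if the patient dies within 30 days, so an unrecorded death between discharge and day 30 would leave a favourable score in place.

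**Working it through.** **Plan's own figure.** The protocol gives no event count or power for survival. Its only sample size is for bilirubin at 72 h: difference 5 mg/dl, SD 5 mg/dl, two-sided 5%, 17 per arm. The two-sample t-test gives 80.7% power at 17 per arm, so that figure reproduces. Nothing below touches it.

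**The passages side by side.**
- Fig. 3 caption and Clinical data: survival to day 90, all patients.
- Clinical data: all data from the electronic files.
- Participant retention and follow-up: no specific follow-up, no measures.

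The first and third conflict. The second does not repair the conflict, because it names no source outside the hospital.

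**How many patients could be of unknown status.** Inputs:
- N = 34, the two arms of the main comparison (2 × 17).
- Day-30 mortality m = 22% to 77%, borrowing the 28-day range in the Introduction; 50% is an assumed middle value.
- Assumed: a share f = 30% to 90% of day-30 survivors has left hospital with status not in the chart.

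Unknown = 34 × (1 − m) × f:
- m = 22%: 34 × 0.78 × 0.3 = 8.0, up to 34 × 0.78 × 0.9 = 23.9
- m = 50%: 5.1 to 15.3
- m = 77%: 2.3 to 7.0

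**If they are counted as alive.** Assume also that d = 20% of day-30 survivors die by day 90, in or out of hospital. True day-90 survival is (1 − m)(1 − d). The reading is (1 − m)(1 − d(1 − f)). The error is (1 − m) × d × f.

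| m | True | Reading, f = 30% to 90% | Error (points) |
|---|---|---|---|
| 22% | 62.4% | 67.1% to 76.4% | 4.7 to 14.0 |
| 50% | 40.0% | 43.0% to 49.0% | 3.0 to 9.0 |
| 77% | 18.4% | 19.8% to 22.5% | 1.4 to 4.1 |

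**If they are censored at discharge.** All inputs here are assumed:
- a constant in-hospital hazard λ = ln 2 / 28 = 0.0248 per day
- discharge time D gamma-distributed with mean 20 days and shape 2, 4 or 9, density g
- mortality q = 10% or 25% from discharge to day 90, at constant hazard

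Kaplan-Meier at day 30 then estimates exp(−30λ) = 0.5^(30/28) = 47.6%, whatever happens after discharge. True survival is exp(−30λ) × P(D > 30) + ∫₀³⁰ g(t) exp(−λt) (1 − q)^((30 − t)/(90 − t)) dt.

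| Shape | q | True day-30 survival | Error (points) |
|---|---|---|---|
| 2 | 10% | 65.2% | −17.7 |
| 2 | 25% | 63.1% | −15.5 |
| 4 | 10% | 62.8% | −15.2 |
| 4 | 25% | 60.9% | −13.4 |
| 9 | 10% | 61.1% | −13.6 |
| 9 | 25% | 59.5% | −11.9 |

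True 28-day mortality in this model is 34% to 40%, not 50%, because discharge ends exposure to the in-hospital hazard.

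In the same model, counting discharged patients as alive reads day-90 survival as 61.8% to 64.3%, against a true 46.3% to 57.8%. Matched case by case, the error is 6 to 16 points up.

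**The case against.** The retention sentence may mean only that there are no follow-up visits and no retention programme. The timeline figure and the schedule of assessments are not visible here, the consent pages were removed, and an article may leave the mechanics of a day-90 contact to the full protocol. Detailed censoring rules belong in an analysis plan. Confirmatory testing is restricted to bilirubin at 72 h, and with 17 patients per arm survival estimates will be imprecise anyway.

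Much of this stands. It limits the consequence and rules out any claim that a censoring rule is missing. It does not remove the conflict: the article addresses follow-up and says that none is planned, which is a statement and not an omission. An analysis plan can define censoring, but it cannot supply vital status that nobody collected.

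Three stronger readings are tempting, and the documents do not support them.
- **A reader might infer that 30-day and 90-day survival contradict each other.** The Fig. 3 caption reconciles them: a 30-day study period with survival extended to day 90. Both can be read from one curve.
- **A reader might infer that discharged patients will be censored at discharge or taken as alive.** No section says either.
- **A reader might extend the censoring illustration to day 90 and report a very large error.** In that model at most about 3 of 20,000 patients would still be at risk at day 90 (20,000 × P(D > 90) × exp(−90λ)), so the Kaplan-Meier value there is tail noise.

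**Conclusion.** The point holds as a contradiction between the retention section and the day-90 commitment, made worse by a data source limited to the hospital's charts. Followed literally, vital status after discharge may be missing for the most relevant secondary endpoint and for the three free-day endpoints.

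The direction of error depends on a handling rule that the documents do not give. Its size depends on discharge and later-death rates that they do not give either. Under the assumptions above it is about 12 to 18 points down at day 30 with censoring at discharge, or roughly 1 to 16 points up at day 90 with discharged patients counted as alive. The upward error is smallest when in-hospital mortality is near the top of the quoted range. The primary endpoint and its sample size are unaffected. The correction should be made, but it does not threaten the trial's confirmatory result.

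**What to change.** - In Participant retention and follow-up, replace the sentence with a vital-status check at day 30 and day 90 for every patient no longer in hospital.
- Name the source, for example a call to the patient, the representative or the family doctor, and amend the Clinical data section so that charts are not the only source. Confirm that the consent covers this contact.
- In Secondary endpoints and the statistical methods, state that survival time is followed to day 90, that 30-day survival is read from the same curve, and that patients are censored at the last date confirmed alive or at day 90.

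The cost is one or two short contacts for at most 51 patients, by the existing study team, and a wording change if the consent does not already cover it.
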